## Abstract

**Introduction:**

Oxaliplatin-induced chronic peripheral neuropathy (OICPN) is a prevalent side effect experienced by patients receiving chemotherapy that primarily manifests as ongoing numbness in the limbs that can persist after treatment ends. This condition significantly diminishes quality of life and frequently leads to dose reduction or early treatment cessation, compromising antitumor efficacy. However, a universally accepted and effective approach for the prevention or treatment of OICPN is currently unavailable. In our clinical observations, we have noted that warm acupuncture may relieve the symptoms of patients experiencing OICPN. Consequently, we propose this randomized controlled trial (RCT) to rigorously assess the safety and effectiveness of warm acupuncture for OICPN patients with the goal of providing preliminary evidence for its use in clinical settings.

**Methods and analysis:**

This study is a multicentre, randomized, controlled clinical trial involving 84 patients diagnosed with OICPN. Participants will be randomly divided into two groups in a 1:1 ratio to receive either standard care alone or warm acupuncture plus standard care. This regimen will include 16 sessions, with treatments occurring twice a week for the first month and once a week for the subsequent 2 months. All participants will complete the 12-week program and one-year follow-up. Outcomes will be assessed by blinded evaluators. The primary outcome is neurotoxicity graded by the National Cancer Institute Common Terminology Criteria for Adverse Events (NCI-CTCAE) version 4.0. Secondary outcomes include the European Organization for Research and Treatment of Cancer Quality of Life Questionnaire–Chemotherapy-Induced Peripheral Neuropathy 20-item scale (EORTC QLQ-CIPN20) and the European Organization for Research and Treatment of Cancer Quality of Life Core 30 Questionnaire (EORTC QLQ-C30), measured at baseline, week 2, month 1, post-treatment, and during follow-up.

**Clinical trial registration:**

https://www.chictr.org.cn/index.html, ChiCTR2400082506.

## Background

1

Oxaliplatin is a platinum-based chemotherapy drug from the third generation that is commonly used to treat different types of solid tumors (1). FOLFOX chemotherapy, which pairs 5-fluorouracil with oxaliplatin, along with the XELOX chemotherapy, which combines capecitabine and oxaliplatin, are recognized as primary standard treatment options for colorectal cancer (2). The main adverse effects of oxaliplatin include peripheral neuropathy, myelosuppression, and gastrointestinal reactions (3).

Oxaliplatin-induced chronic peripheral neuropathy (OICPN) is a significant dose-limiting side effect that can hinder some patients’ ability to adhere to their treatment plans, often leading to reduced dosages or the complete cessation of chemotherapy, which in turn diminishes its effectiveness in clinical settings (4, 5).

Chronic peripheral neuropathy resulting from oxaliplatin affects approximately 40% of individuals undergoing treatment (6). This condition typically manifests as bilateral numbness and pain in a glove-and-stocking pattern, along with slight difficulties in fine motor skills and sensory ataxia. It follows a cumulative, dose-dependent trajectory, generally emerging and intensifying after approximately 3 months of ongoing therapy. Neuropathy classified as Grade 3 is observed in 50% of patients who have received a total dose of 1,170 mg/m^2^ (7). This condition often persists and may worsen even after treatment has ended, a phenomenon known as coasting (8). Research indicates that nearly 60% of patients report ongoing neuropathic symptoms following their last chemotherapy session, with 19% experiencing severe symptoms 18 months later (9). Additionally, 31% of patients continue to endure OICPN 5 years after completing chemotherapy (10). These symptoms significantly diminish the quality of life of cancer survivors.

Warm acupuncture integrates traditional acupuncture with moxibustion by igniting moxa wool placed on the handle of the needle. The heat generated from the burning moxa travels through the needle to stimulate specific acupoints. This method is known to alleviate cold, clear blockages, boost yang energy, enhance overall qi, and improve blood flow. Additionally, the heat and distinctive volatile substances released during moxa burning are thought to improve microcirculation and bodily functions, stimulate various systems, and increase tissue metabolism and heat generation. Earlier research has suggested the potential benefits of warm acupuncture for OICPN (30–33). However, these investigations often suffer from methodological flaws, including being conducted at a single centre (30, 31). Common issues in previous studies include small participant groups, brief follow-up periods, varying outcome measures, and a lack of standardized procedures (30–33). We have developed a multicentre, randomized controlled trial for colorectal cancer patients to overcome these challenges. This trial will include multiple follow-up visits over a comprehensive 12-month timeframe, implement a rigorously standardized warm acupuncture protocol, and utilize internationally accepted neurotoxicity grading scales and quality-of-life questionnaires for evaluation. The goal of this research is to deliver empirical evidence on the effectiveness of warm acupuncture in managing oxaliplatin-induced neurotoxicity, supported by both clinical findings and theoretical insights.

## Methods and analysis

2

### Study design

2.1

This clinical trial is designed as a randomized, controlled study with the assessors blinded to the treatment allocation. It will be conducted in six medical facilities throughout China, including the Jiangsu Province Hospital with Integration of Chinese and Western Medicine, Huai’an Hospital of Traditional Chinese Medicine, Yancheng Hospital of Traditional Chinese Medicine, Jiangyin Hospital of Traditional Chinese Medicine, Dongtai Hospital of Chinese Medicine, and Nanjing Lishui District Hospital of Traditional Chinese Medicine. The recruitment of participants will occur simultaneously in outpatient settings and hospital wards.

The Institutional Ethics Committee at the coordinating centre has reviewed and granted approval for this study, as indicated by the approval number 2024-LWKYZ-008, which remains valid until February 23, 2027. Prior to participation, all individuals will provide written informed consent. Participants who are enrolled will receive complimentary warm acupuncture treatment. The methodology in this trial is meticulously organized, ensuring that ethical standards are met. The protocol aligns with the Standard Protocol Items: Recommendations for Interventional Trials (SPIRIT) guidelines to uphold scientific integrity (35). Additionally, the results will be reported in accordance with the relevant Consolidated Standards of Reporting Trials (CONSORT) extension guidelines, ensuring rigorous quality control throughout the research (36).

Participants who meet the criteria will be randomly divided into two groups, with an equal ratio of 1:1, assigning them to either the warm acupuncture group or the standard care group. All individuals will participate in a treatment phase lasting 12 weeks, followed by a follow-up period of 1 year. Medical statisticians will analyse the outcome data. This trial has been officially registered with the Chinese Clinical Trial Registry (Registration number: ChiCTR2400082506). The flow of this study is illustrated in Figure 1, while a comprehensive schedule for enrolment, interventions, and assessments is provided in Table 1.

**Figure 1 fig1:**
[figure not shown]
Flow diagram of this study. A total of 84 participants will be included in this study and will be randomized (1:1) to two groups: (1) A standard care group with only typical protective guidelines and (2) a warm acupuncture group with the same standard care and a 12-week warm acupuncture regimen. All participants will complete the 12-week intervention and a subsequent one-year follow-up.

**Table 1 tab1:** Schedule of enrolment, interventions, and assessments.

Study Schedule	Study period								
	Baseline	Discharge				Follow-up			
Timepoint	T0	T1	T2	T3	T4	T5	T6	T7	T8
Week	0	2	4	8	12	16	24	36	60
Enrollment									
Eligibility screen	**×**								
Informed consent	**×**								
Demographics	**×**								
Medical history	**×**								
Physical examination	**×**								
Laboratory examination	**×**								
CT/MRI	**×**								
ECG	**×**								
Neurological evaluation	**×**								
Interventions									
Standard care group		3 months of treatment							
Warm acupuncture group		3 months of treatment							
Assessment									
NCI-CTCAE V4.0	**×**	**×**	**×**	**×**	**×**	**×**	**×**	**×**	**×**
EORTC QLQ-CIPN20	**×**	**×**	**×**	**×**	**×**	**×**	**×**	**×**	**×**
EORTC QLQ-C30	**×**	**×**	**×**	**×**	**×**	**×**	**×**	**×**	**×**

### Inclusion criteria

2.2

Participants who met all of the following requirements were considered for inclusion: (1) Aged 18–85 years; (2) Completion of chemotherapy (at least 3 months prior) using the mFOLFOX6 or XELOX regimen*; (3) Presence of chemotherapy-induced peripheral neuropathy with a neurotoxicity grade ≥2 according to the NCI-CTCAE version 4.0; (4) Absence of severe cardiac, hepatic, renal, or hematopoietic system impairments; (5) Karnofsky Performance Status (KPS) score ≥60 and an expected survival of ≥6 months; (6) Absence of any cognitive or mental health issues; possesses typical verbal skills to effectively articulate symptoms and the overall state; (7) Provision of written informed consent.

$$\begin{array}{l} {}*\text{mFOLFOX}6—\text{oxaliplatin},\text{leucovorin},\text{fluorouracil};\\ \text{XELOX}—\text{oxaliplatin},\text{capecitabine} \end{array}$$

### Exclusion criteria

2.3

Patients were excluded if they had: (1) A record of other cancerous tumors in the last 5 years, excluding those with carcinoma *in situ* that has been completely treated; (2) Presence of other neurological disorders (e.g., diabetic neuropathy and infectious or toxic neuropathy); (3) Current use of other medications with known neurotoxicity; (4) Medications are currently being utilized for the prevention and management of neuropathic pain, including duloxetine, gabapentin, pregabalin, venlafaxine, and mecobalamin; (5) Pregnancy, planned pregnancy, or lactation; (6) Presence of psychiatric or consciousness disorders impairing cooperation; (7) Severe skin diseases or ulceration occurring on the limbs; (8) Having received acupuncture treatment for any indication within the past 1 month; (9) Currently participating in any other clinical trial of a drug.

### Sample size calculation

2.4

This study employs a randomized controlled trial methodology to assess the effectiveness of warm acupuncture for alleviating peripheral neuropathy caused by oxaliplatin, comparing a warm acupuncture cohort with a standard care cohort. The main measure of interest is the neurotoxicity level, which will be evaluated using the NCI-CTCAE version 4.0 criteria. Based on previous research, a treatment response is indicated by a decrease of one or more grades in neurotoxicity (37). The expected response rates for the two groups are 0.8 and 0.47, respectively. Utilizing a standard formula for the comparison of two proportions, with a two-tailed alpha level of 0.05 and a power of 80% (*β* = 0.2), a minimum of 33 participants is necessary for each group. Considering an estimated dropout rate of approximately 20%, the target sample size is established at no less than 40 participants per group. Consequently, the overall sample size for this investigation is set at 84 participants, with 42 in each group.

### Randomization and allocation concealment

2.5

A statistician who is not part of the clinical trial will create the randomization sequence utilizing SAS software, version 9.4 (SAS Institute Inc., Cary, NC, United States). This sequence will utilize a block randomization approach with block sizes of 4, 6, or 8, organized by study centre. The resulting randomization list will then be uploaded to an Interactive Web Response System (IWRS). After screening an eligible participant and obtaining informed consent, the site investigator will access the IWRS to enter the participant’s basic identifiers along with the centre code. The system will then automatically generate a unique randomization number and assign the appropriate treatment group, ensuring that allocation remains fully concealed. Regular audits of IWRS procedures and documentation will be conducted to ensure consistent implementation of the allocation workflow across all centers.

### Data collection and monitoring

2.6

This study will employ a uniform electronic data capture (EDC) platform for managing data. All site research coordinators will receive centralized training on uniform screening procedures and case report form completion standards. Trained research coordinators will independently enter all information from the case report forms into the EDC system. The platform will automatically conduct logic and range validations. Source data verification will follow a set monitoring strategy, with clinical research associates conducting frequent on-site inspections at each participating site to maintain operational uniformity and confirm the alignment between the electronic data and the original medical records.

To further ensure treatment fidelity, these on-site inspections will include direct observation of warm acupuncture sessions to verify protocol adherence. In addition, a detailed Standard Operating Procedure (SOP) manual has been developed for this trial to specify all operational parameters and minimize inter-practitioner variability. Prior to trial initiation, all acupuncturists will receive centralized training on the SOP and will be certified only after demonstrating consistent competency in performing the standardized warm acupuncture procedures. These on-site inspections will also monitor randomization and enrollment procedures to ensure consistent implementation of the IWRS-based allocation workflow across all centers.

The Jiangsu Province Hospital with Integration of Chinese and Western Medicine will oversee this trial. An independent Data Monitoring Committee (DMC) will be formed to uphold the integrity and safety of this trial. This committee will regularly assess the gathered data and review the safety and efficacy outcomes of the research. Comprising specialists in oncology, statistics, and research methods, the committee will have the authority to request unblinding during both interim and final evaluations. Any serious adverse events must be reported to the principal investigator, the ethics committee, and the sponsor within a 24-h timeframe, while ongoing safety monitoring will be facilitated through the EDC system.

### Blinding

2.7

Given the unique characteristics of acupuncture techniques, employing a double-blind approach is impractical in this study. Both the practitioners providing the acupuncture and the patients receiving it will know which treatment they are assigned. The processes for administering the treatment and assessing the results will be distinctly divided to reduce any possible bias. Practitioners conducting the warm acupuncture will not be involved in the evaluation of the treatment results. During the course of the study, the individuals assessing outcomes and the statistician analyzing the data will not have knowledge of the treatment assignments.

## Interventions

3

### Standard care group

3.1

Participants in the standard care group will be instructed to: (1) Avoid contact with either cold or hot water; (2) Wear gloves and socks to protect their hands and feet; (3) Avoid direct contact with metal objects; (4) Refrain from alcohol consumption; (5) Avoid strenuous exercise such as long-distance hiking.

### Warm acupuncture group

3.2

Alongside standard care, patients will receive warm acupuncture therapy. They will lie on their backs with the treatment areas properly exposed and sanitized. Acupuncture will be applied to the following specific points: Quchi (LI11), Waiguan (TE5), Hegu (LI4), and Baxie (EX-UE9) on the arms; Guanyuan (CV4) on the abdomen; and Zusanli (ST36), Sanyinjiao (SP6), Taichong (LR3), and Bafeng (EX-LE10) on the legs. A qualified practitioner with 3 years of experience will perform needling using single-use stainless steel needles (0.25 mm × 40 mm, sourced from Suzhou Hualun Medical Apparatus Co., Ltd., China). The insertion depth and angle will follow the guidelines in The Science of Acupuncture, utilizing a consistent reinforcing–reducing technique to prioritize patient safety and treatment efficacy. Once the deqi sensation is achieved, a 27-mm moxa stick (from Nanyang Baicaotang Natural Moxa Products Co., Ltd., made from 10-year aged moxa, measuring 18 mm × 27 mm) will be placed on the needle handles at Zusanli (ST36) and Guanyuan (CV4). The moxa stick will be held approximately 20 mm above the skin, separated by a small paper sheet. The base of the moxa stick will be ignited and allowed to burn out completely, after which the paper will be removed while the moxa remains on the needle. The needles will generally remain in place for 20 to 30 min before the ash is cleared and the needles are removed. This treatment will occur twice weekly during the first 4 weeks and once weekly from weeks five to 12, with each session lasting 30 min, completing a full 12-week course. This tapered frequency schedule was designed to achieve rapid symptom control during the initial intensive phase and to consolidate therapeutic effects during the subsequent maintenance phase.

### Outcomes

3.3

Medical professionals will evaluate neurotoxicity at several key intervals: at the start of treatment; at 2 weeks, 4 weeks, and 8 weeks after treatment; and at 1 month, 3 months, 6 months, and 12 months after the initial treatment cycle. The assessment will utilize the NCI-CTCAE version 4.0, along with the EORTC QLQ-CIPN20 and EORTC QLQ-C30 scales. Safety will be monitored by recording any adverse events in accordance with the NCI-CTCAE version 4.0 guidelines.

#### Primary outcome measure

3.3.1

##### Neurotoxicity grading

3.3.1.1

Peripheral neurotoxicity will be assessed using the NCI-CTCAE version 4.0. This classification categorizes neuropathy into four distinct grades: Grade 1 indicates the presence of areflexia or paraesthesia that does not affect functionality; Grade 2 involves sensory changes or paraesthesia that disrupts function but does not impact daily living activities; Grade 3 refers to sensory changes or par-aesthesia that hinders daily living activities; and Grade 4 represents a severe sensory–motor neuropathy that greatly impairs daily living activities. To ensure the reliability of the CTCAE grading, all outcome assessors will receive standardized training on the CTCAE version 4.0 criteria prior to trial initiation, and periodic quality checks will be performed to minimize inter-evaluator variability. If discrepancies are identified, the grading will be reviewed and adjudicated by a designated specialist.

#### Secondary outcome measures

3.3.2

##### Neurotoxicity symptoms

3.3.2.1

These symptoms will be assessed using the EORTC QLQ-CIPN20. The intensity of chemotherapy-induced peripheral neuropathy is measured through the cumulative score obtained from the EORTC QLQ-CIPN20 questionnaire. This validated patient-reported outcome measure (PROM) is well-established for evaluating peripheral neuropathy, especially chemotherapy-induced peripheral neuropathy. Comprising 20 questions that address sensory, motor, and autonomic functions, the questionnaire utilizes a 4-point Likert scale, with scores ranging from 1 to 4. The total score can vary between 20 and 80, which is subsequently converted to a scale of 0 to 100. A higher score reflects a more severe level of neurotoxic symptoms.

##### Severity of neuropathy and quality of life

3.3.2.2

These parameters will be measured using the EORTC QLQ-C30, a questionnaire developed by the European Organization for Research and Treatment of Cancer.

The EORTC QLQ-C30 is a prominent tool used globally to evaluate quality of life in oncology clinical research (38). It includes five functional dimensions, physical, role, cognitive, emotional, and social quality of life, along with three symptom dimensions (fatigue, pain, and nausea/vomiting), six individual symptom assessments (dyspnoea, appetite loss, insomnia, constipation, diarrhea, and financial issues), and a global health status measure. Higher scores in the functional dimensions, which assess aspects such as balance and daily activities, reflect an improved quality of life, similar to what is measured by the Fugl–Meyer and Berg balance scales. In contrast, higher scores in the symptom dimensions and individual assessments, such as those related to pain or depression, indicate a decline in quality of life or a greater symptom burden.

#### Safety assessment

3.3.3

The evaluation of adverse events will be conducted using the NCI-CTCAE version 4.0, released on June 14, 2010. This terminology serves as a framework for reporting adverse events. Following each treatment session, an additional safety assessment will be performed to record any side effects experienced by participants in both treatment groups.

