Additional statistical details are predefined. In the primary models, we will adjust for key baseline covariates that display an imbalance (*p* < 0.1) or possess established prognostic significance (e.g., number of chemotherapy cycles). If a significant group-by-time interaction is identified, Bonferroni-corrected *post hoc* pairwise comparisons will be conducted. Missing data, assumed to be missing at random, will be managed using the likelihood-based estimation inherent to linear mixed models; the robustness of findings will be assessed through sensitivity analyses, including the last observation carried forward method. All adverse events will be summarized using descriptive statistics, and between-group differences in incidence rates will be evaluated using the Chi-square test or Fisher’s exact test, as appropriate. For participants who withdraw from the study, the primary efficacy analysis will follow the Intention-to-Treat (ITT) principle, with linear mixed models handling missing data under the Missing at Random assumption. A Per-Protocol (PP) analysis will be conducted as a sensitivity measure. All withdrawals and protocol deviations will be recorded with detailed reasons.

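### The extra side-effect assessment is triggered by treatment sessions, which only the warm acupuncture arm has, so the planned between-group test of adverse event incidence rests on unequal ascertainment

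*Protocol article*

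**What the plan says.** Section 3.3.3 (Safety assessment) adds a check to the general adverse event recording: "Following each treatment session, an additional safety assessment will be performed to record any side effects experienced by participants in both treatment groups".

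The two arms differ in whether they have sessions. For warm acupuncture, section 3.2 says "This treatment will occur twice weekly during the first 4 weeks and once weekly from weeks five to 12", and the abstract says "This regimen will include 16 sessions". For the control arm, section 3.1 begins "Participants in the standard care group will be instructed to" and lists five self-care precautions. The Figure 1 legend describes "A standard care group with only typical protective guidelines". No control session is described anywhere.

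Section 4.2 plans a comparison of the arms: "between-group differences in incidence rates will be evaluated using the Chi-square test", with Fisher's exact test as the alternative.

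Two other places cover the trial as a whole. Section 3.3 says "Safety will be monitored by recording any adverse events in accordance with the NCI-CTCAE version 4.0 guidelines", in the same paragraph as the scheduled visits. Section 2.6 provides for continuing safety monitoring through the EDC system. Section 4.1 limits the safety analysis set to participants who had at least one warm acupuncture session.

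**The concern.** Section 3.3.3 promises the additional assessment in both groups, but on a trigger that one group never meets. A site following the text would question each acupuncture patient after every session and would have no matching occasion for a control. The alternative is to improvise, and six centres may improvise differently.

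The assessment is meant to pick up any side effect, not only needling or moxa effects. Background symptoms in cancer survivors, such as fatigue or insomnia, would therefore be noted more readily in the acupuncture arm. The incidence test in section 4.2 would then partly measure how often patients were asked. Safety is a stated aim in the abstract, and an apparent excess of harm produced this way would count against the trial's own intervention. It cannot be undone after data collection unless the way each event was found has been recorded.

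**Working it through.** **Session count.** From section 3.2: 2 × 4 + 1 × 8 = 16, which agrees with the abstract. Section 4.1 sets the per-protocol threshold of 80% at 13 sessions (0.8 × 16 = 12.8, rounded up). So the article itself uses the word for acupuncture visits.

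**Session-triggered assessments per patient.** Warm acupuncture 16, standard care 0.

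**Contacts shared by both arms.** Table 1 gives T1–T4 (weeks 2, 4, 8, 12) during treatment and T5–T8 (weeks 16, 24, 36, 60) afterwards. If adverse events are asked about at T1–T4, contacts to week 12 are at most 16 + 4 = 20 against 4. If those visits fall on session days, they are 16 against 4.

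**Effect on the test.** The documents give neither an expected adverse event incidence nor the share of events that each form of questioning would find. The following are therefore assumptions:

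- no true difference between arms, and 42 patients per arm (section 2.4);
- recorded incidence *a* in the acupuncture arm of 18.2%, 33.2% or 45.6%. These values are 1 − (1 − p)^20 for p = 1%, 2% and 3% per contact, and serve only to span a range;
- recorded incidence in controls of *s* × *a*, where *s* is the control arm's capture relative to the acupuncture arm.

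The rejection probability is the sum, over all pairs of counts (i, j), of Bin(i; 42, a) × Bin(j; 42, s·a), taken where the two-sided Fisher p-value is at most 0.05.

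| Relative capture s | a = 18.2% | a = 33.2% | a = 45.6% |
|---|---|---|---|
| 1.0 (equal) | 2.9% | 3.0% | 3.7% |
| 0.9 | 3.2% | 3.9% | 5.3% |
| 0.7 | 6.6% | 12.3% | 20.0% |
| 0.5 | 15.2% | 34.3% | 52.4% |

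The uncorrected chi-square test, the other test named, shows the same pattern. At a = 30% it rejects in 5.1% of trials with equal capture, and in 6.1%, 15.9% and 38.6% at s = 0.9, 0.7 and 0.5.

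The result depends almost wholly on *s*. At 0.9 the inflation is negligible; at 0.5 it is serious.

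**The case against.** The best defence is that control events are recorded. Section 3.3 records adverse events alongside visits that both arms attend, section 2.6 adds monitoring through the EDC, and section 3.3.3 calls the session check additional, so a base collection exists. None of these is restricted by arm. This stands. A reader might infer that control events go uncollected, and the documents do not support that.

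A second defence is that section 3.3.3 names both groups, and that the full protocol may say how controls are contacted. That may be so, but the stated trigger still has no counterpart in the control arm. Table 1 shows three months of treatment for both arms, which gives a duration and not sessions. The conflict lies in the wording given. By contrast, the lack of an adverse event row in Table 1 is a detail that a condensed article may leave out, and it carries no weight here.

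A reader might also infer a very high false-positive rate. Treating 20 and 4 contacts as independent chances of recording an event, at 1%, 2% or 3% each, gives rejection by Fisher's test of 43%, 80% and 93%. The documents do not support those figures. That model lets a visit recover nothing from the interval since the previous one, so controls capture only 22% to 25% of what the acupuncture arm captures. The count of 20 is also an upper bound; with 16 against 4 the same model gives 25%, 60% and 79%.

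Finally, some of what sessions reveal is real harm from the procedure. Bruising, for example, may be a true effect of needling, and a difference there need not be an artefact. That is a reason to keep the session assessment.

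**Conclusion.** The point holds as an internal conflict with a consequence for one analysis. Section 3.3.3 sets a session trigger for both groups, section 3.1 and the Figure 1 legend give controls no sessions, and section 4.2 tests the resulting incidences. Followed as written, this means 16 additional assessments per acupuncture patient and none per control, with bias towards more recorded events under acupuncture.

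The direction is clear, but the size is not known. On the assumptions above, false rejection ranges from about 3–5% at 90% relative capture, through 7–20% at 70%, to 15–52% at 50%, against 3–4% with equal capture. The efficacy analyses are not touched. The plan should be changed because safety is a stated aim and the remedy is cheap.

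**What to change.** - **Section 3.3.3:** ask about adverse events since the last visit, with the same question in both arms, at the shared visits T1–T8. Keep the post-session assessment and describe it as applying to the warm acupuncture arm.
- **Section 4.2:** base the between-group test on visit-collected events. Session-related harms that a patient reports at a visit still count. Report events found only at post-session assessments descriptively for the warm acupuncture arm, per patient and per session.
- **Section 4.1:** reconcile the safety set with section 4.2, so that the set used for the comparison includes the standard care arm. Read literally, the present definition leaves the test without a control group, and the other two changes would not give a usable comparison.

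The cost is a few sentences across the three sections and an EDC flag showing how each event was found. No visits are added. The downside is that some minor events found only at sessions leave the comparative test, though they are still reported.
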